### Monitoring and harms

Study monitoring will be done by an external site monitoring institute (AMS – Advanced Medical Services GmbH, Mannheim, Germany) being entirely independent of the institutions and investigators involved in the study conduct. Systematic quality assurance and control will include a monitoring plan, regular on-site audits at every study center, partial source data verification, and site management. (Serious) adverse events/reactions will be monitored throughout the study to assess the safety of the trial and manage participant risk. Serious adverse events are defined as any harmful disease or injury that leads to hospital admission or death or resulted in persistent disability or incapacity. (Serious) adverse events (potentially) related to study participation will be reported to the ethic committees. ll participants enrolled in the study are covered by a subject and travel accident insurance.

### Statistical analysis

Group differences in the primary outcome of LLFDI-FC at month 12 (T_2_) will be analyzed in a confirmatory manner using a two-sided *t*-test for independent samples. In addition, linear regression analysis will be used to explore the group effect on LLFDI-FC at T_2_, adjusted for the baseline values and other covariates (e.g., age, sex, care need or comorbidities). Both analyses will also be conducted in an explorative manner after 6 months (T_1_) to evaluate time effects. Potential time effects over the total 12-month study period will be examined by analysis of covariance for repeated measures. The second, subordinated primary endpoint UAB-LSA will be analyzed using the same methods as described before for the LLFDI-FC. Secondary outcomes and safety issues at the T_1_ and T_2_ will be compared between the two treatment groups using *χ*^2^-tests or Fisher exact tests, Mann-Whitney *U* tests, *t*-tests for independent samples, multiple regression analyses as appropriate. To investigate whether specific subgroups (e.g., age, sex, functional baseline status) in IG benefit more from the PromeTheus program compared with their counterparts in CG, exploratory subgroup analyses will be performed by inclusion of interaction terms (subgroup × treatment) in each single statistical model. All main analyses will be conducted according to intention-to-treat principle, with all participants randomized after baseline assessment, regardless of subsequent treatment adherence, withdrawal from the study, or protocol deviation. Missing data will be imputed using multiple imputation by fully conditional specification method performed with SAS PROC MI. All statistical analyses will be performed with SAS version 9.4 (Statistical Analysis Software, SAS Institute Inc., Cary, North Carolina, USA) or R version 4.0.2 (R Foundation for Statistical Computing, Vienna, Austria).

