### Sample size

The sample size calculation was performed for a group comparison at 12 months (T_2_) in the LLFDI-FC score as the primary outcome of the study. Based on the baseline LLFDI-FC score of 69 points with a standard deviation of 15 points reported in the LiFE study [81] for an elderly population similar in frailty to the target sample of the PromeTheus study, and the minimal clinically important difference of 5 points reported for the LLFDI-FC in community-dwelling older adults with mobility limitations [82], 143 participants per group are required to achieve a power of 80% at a significance level of 5% using a 2-tailed *t*-test for independent samples. Considering a dropout rate of 20%, as observed in the LiFE study [81], the sample size increases to 179 participants for each group. To account for additional variance due to the multicenter study design, the sample size was further increased by 10%, resulting in a final sample size of 199 participants (rounded *n* = 200) per group.

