### Randomization and blinding

After the baseline assessment, participants will be randomly allocated to the IG or CG using computer-generated block randomization with a 1:1 allocation ratio stratified by study site and baseline CFS score. The randomization will be undertaken externally at the Institute for Epidemiology and Medical Biometry, Ulm University, Ulm, Germany using the randomization program ROM [84]. Participants will be informed about the randomization outcome by the physiotherapists at the phone call for scheduling the first home visit (IG: WEBB, CG: one-time counseling session). All primary and secondary outcome assessments will be undertaken by assessors blinded to group allocation. Data that identify group allocation such as training adherence (EARS, training diaries) will be collected by the unblinded physiotherapists.

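### The confirmatory t-test at month 12 uses neither the baseline score nor the randomisation strata; a prespecified ANCOVA would gain precision at no cost (should-fix)

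*Protocol article*

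**What the plan says.** All references are to the protocol article.

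- **Statistical analysis, confirmatory test.** The month-12 (T2) comparison of LLFDI-FC between the arms "will be analyzed in a confirmatory manner using a two-sided" unpaired t-test. No covariate or stratum enters it.
- **Statistical analysis, adjusted model.** As a supplement only: "linear regression analysis will be used to explore the group effect on LLFDI-FC at T_2_, adjusted for the baseline values and other covariates". The covariates are given as examples ("e.g., age, sex, care need or comorbidities"); site and CFS are not among them.
- **Statistical analysis, second primary endpoint.** The LSA, described as subordinated, is analysed by the same methods.
- **Randomization and blinding.** Allocation is in blocks, "with a 1:1 allocation ratio stratified by study site and baseline CFS score".
- **Table 3 and Participant timeline.** LLFDI-FC and LSA are both measured at T0, and randomisation follows the baseline assessment.
- **Sample size.** The calculation uses a two-tailed t-test for independent samples with SD 15, difference 5, 80% power and 5% significance. It gives 143 per group, then 179 after 20% dropout and 199 (rounded to 200) after a further 10% for the multicentre design.

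**The concern.** The plan collects the variable likely to predict the month-12 score best, the same score at baseline, and then leaves it out of the one analysis that decides the trial. It also restricts the randomisation by site and CFS without reflecting this in the confirmatory test. These are two different matters.

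- **Baseline score.** Leaving it out gives a less precise estimator. Its standard error is correct for that estimator, but larger than it need be.
- **Strata.** Stratified blocks remove most of the between-arm variation due to site and CFS, yet the t-test still counts that variation in its standard error. If the strata predict the outcome, the reported standard error is too large and the test runs below its nominal 5%.

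At stake is a missed or blurred effect, not a false positive. The plan will produce two estimates of the same contrast. If the adjusted one is convincing and the t-test is not, the less precise result is confirmatory and the better one can only be called exploratory. Changing their roles after unblinding would not be credible.

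**Working it through.** **Inputs from Sample size:** SD 15; difference 5; two-sided 5%; dropout 20%; 200 per arm, hence 200 × 0.8 = 160 analysed per arm. **Assumed, because the document does not give them:** the correlation r between the baseline and month-12 score (0.3, 0.5, 0.7), and the share R² of outcome variance explained by the strata (10%, 20%).

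1. **The plan's own figure.** For a standardised difference of 5/15 = 0.333, the noncentral t calculation gives 142.2, so 143 per group. Then 143/0.8 = 178.75, so 179, and 179/0.9 = 198.9, so 199. All three stated figures reproduce.

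2. **Unadjusted test.** SE = 15 × √(2/n). With n = 160 this is 1.68 points. The 95% CI half-width is 1.96 × 1.677 = 3.29 points and power is 84.4%. With n = 143, power is 80.2%.

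3. **Adjusting for the baseline score.** The SE is multiplied by √(1 − r²).

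| Assumed r | SE, n = 160 | CI half-width | Power, n = 160 | Power, n = 143 | n per arm for 80% (normal approximation) |
|---|---|---|---|---|---|
| none | 1.68 | 3.29 | 84.4% | 80.2% | 142 |
| 0.3 | 1.60 | 3.14 | 87.6% | 83.8% | 129 |
| 0.5 | 1.45 | 2.85 | 93.0% | 90.0% | 106 |
| 0.7 | 1.20 | 2.35 | 98.6% | 97.6% | 73 |

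The variance falls by r²: 9%, 25% and 49%.

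4. **Ignoring the strata.** With perfect balance within strata, the true SE is the reported one times √(1 − R²), so the actual two-sided type I error is 2Φ(−1.96/√(1 − R²)).
   - R² = 0.10: 1.96/0.949 = 2.07, giving 3.9%.
   - R² = 0.20: 1.96/0.894 = 2.19, giving 2.8%.

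   Balance is not perfect in practice. Simulated stratified randomisation (3 sites × 3 CFS levels, assumed blocks of 4 and an assumed CFS mix) with 20% random dropout gives about 4.4% and 3.2%, with a Monte Carlo error of 0.2 to 0.3 percentage points. If the strata explain nothing, the error stays at about 5%.

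**The case against.** The strongest reply is that nothing here is invalid. Under randomisation the t-test is unbiased and its type I error does not exceed 5%. The trial was sized for exactly this test, and the figures reproduce. This stands, and it is why the point is an improvement and not a fatal flaw.

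Four further replies also carry weight.

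- **The gain rests on assumptions.** At r = 0.3, power rises only from 84.4% to 87.6%. That is true, although every correlation in the range brings some gain.
- **160 per arm is a complete-case count.** The plan imputes missing data for everyone randomised, so the t-test's power lies between 84% (nothing recovered) and a ceiling of 91% (200 per arm). This narrows the room for gain in power. It does not recover the precision lost by leaving the observed scores unadjusted.
- **The covariate list is only illustrative.** Not naming site or CFS there does not exclude them from the exploratory model, and an article may leave such a list to the full protocol or analysis plan. The choice of confirmatory test, however, is stated outright and is not left open.
- **Chance baseline imbalance is not bias.** The t-test's standard error already allows for it, and stratifying on CFS should limit it in a related measure.

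A reader might also infer that the 10% sample-size increase for the multicentre design contradicts a test that ignores site. It does not: adding participants to absorb extra between-site variance is coherent precisely when site is not modelled.

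**Conclusion.** The point holds as a should-fix. The confirmatory analysis of both primary endpoints is valid but less efficient than the data allow.

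- **Baseline score: lost efficiency.** With 160 analysed per arm, power for LLFDI-FC is 84% unadjusted against about 88%, 93% and 99% at assumed correlations of 0.3, 0.5 and 0.7. The CI half-width is 3.29 points against 3.14, 2.85 and 2.35.
- **Strata: overstated standard error.** Type I error is about 4.4% to 3.2% instead of 5% if the strata explain an assumed 10% to 20% of the variance. Some prognostic value is plausible, since CFS grades frailty and LLFDI-FC measures physical function, but the document does not quantify it.

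A reader might infer that the primary analysis is wrong or that the trial is underpowered by design. The document supports neither: on its own inputs the t-test has 80% power at 143 per arm and 84% at 160. Nor does the conservative error rate come from omitting the baseline score; apart from the overlap of that score with the strata, only the ignored strata cause it. The enrolment count under Trial status concerns recruitment and does not bear on the choice of test.

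**What to change.** Before unblinding, swap the roles of the two analyses already planned.

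- **Confirmatory:** ANCOVA of the T2 LLFDI-FC score on group, baseline LLFDI-FC, study site and baseline CFS stratum, with this covariate set fixed in advance. Use the same model for the LSA with its own baseline value, keeping its subordinate position.
- **Sensitivity:** the unadjusted t-test as now described.
- **Sample size:** unchanged. It was calculated without adjustment, so it becomes conservative.

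The cost is a sentence in the protocol and in the analysis plan. No new data, visits or participants are needed, because baseline scores, site and CFS are already recorded before allocation.

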## Discussion

The prevention and management of functional limitations and frailty in old age have become one of the most serious global public health challenges. Current evidence for effective intervention strategies to improve functional, mobility, and frailty status in community-dwelling (pre-)frail older adults is, however, still low [16, 23, 27, 85, 86]. It is becoming increasingly evident that multifactorial, interdisciplinary interventions are more effective than one-dimensional ones [23, 24, 87], and that physical activity plays a crucial role in this context [12, 22, 86]. There is an urgent need for large-scale and well-designed RCTs to evaluate the feasibility, implementation, and (cost-)effectiveness of community-based, multidimensional intervention strategies that make use of existing healthcare resources [16, 23, 34]. We expect to accrue more evidence-based knowledge about such an intervention strategy with this study.

As physical exercise has been identified as a key element for improving function and mobility in community-dwelling (pre-)frail older adults [12, 22, 86], the WEBB program will be implemented as an obligatory PromeTheus intervention component. In addition to the home visits suggested for implementation of the WEBB program [40], participants will receive phone calls from the physiotherapists to provide closer social support for exercise prescription and address barriers and motivational issues more frequently. Indeed, social reinforcement through phone calls has been shown to be an inexpensive and feasible method to increase adherence and effectiveness of home-based exercise programs in frail older adults [88].

Diverse facultative intervention components are initiated following standardized assessments of participants’ individual needs. As recommended [12, 16], to close the gap between research and clinical practice and to broaden the focus to the public health and system levels, the PromeTheus program integrates existing structures of the German healthcare system to implement these components.

An individual’s level of functioning (i.e., activity and social participation) can be influenced by contextual factors [89]. Removing environmental barriers through appropriate home modifications and provision of assistive devices can play an essential role in enabling older adults to “age in place”. Intervention components on person-environment-fit have thus been suggested to be included in comprehensive frailty interventions [16, 24, 90]. Home modifications and assistive devices have also been shown to be effective as single intervention components for maintaining and improving daily functioning, reducing the risk of falls, decreasing costs for personal assistance and healthcare, and increasing community participation in frail older adults [91–93]. Referral to local service providers for home modifications and to GPs for prescribing assistive devices will be initiated when there is a need and willingness of the participants.

Care needs of frail older adults are often complex and span across physical environmental and psychosocial domains. In community settings, insufficient psychosocial support has been identified as the most common self-perceived unmet care need of frail older adults [94]. Such support is therefore strongly recommended in clinical practice guidelines for frailty management [95]. As part of the interdisciplinary team of the PromeTheus intervention, social workers qualified also as long-term care counselors are integrated to offer to counsel on coping with everyday life with a special focus on psychosocial needs and social participation.

Insufficient nutritional intake and frailty are closely related [96]. Community-dwelling (pre-)frail older adults are often malnourished or at risk for malnutrition [97], and the co-occurrence of (pre-)frailty and poor nutrition substantially increases the risk for adverse health outcomes [98]. Participants identified as being malnourished or at risk for malnutrition are provided professional nutritional counseling. Physical exercise combined with nutritional interventions has shown to be particularly effective at reducing frailty and improving physical functioning in (pre-)frail older adults [24, 85–87].

Social isolation and loneliness have been linked to reduced physical functioning and frailty in older adults [17] and identified as risk factors for frailty onset and progression [19, 20]. To promote social participation and reduce loneliness, consideration will be given to referring participants to available local group activities as needed. In fact, social engagement in cultural group activities has been shown to decrease the risk for frailty [99].

We expect that the PromeTheus program will preserve physical function and mobility, reduce adverse behaviors (inactivity, malnutrition, social isolation), and improve contextual conditions, thereby leading to enhanced participation [89]. The LLFDI-FC as a PROM assesses self-reported physical functioning. Such person-centered outcomes providing information on what is meaningful from the perspective of the individual person have rarely been studied in frailty intervention trials, and their use has been recommended to address the current evidence-practice gaps for frailty management [16]. The LLFDI-FC has shown to have a higher predictive value for adverse health outcomes (e.g., hospitalization, falls, low self-reported health) than performance-based measures [71] and the Fried frailty phenotype [100] in older primary care patients. The LSA defined as a second primary outcome is a comprehensive measure of self-reported real-life mobility within the home and community. It assesses how far and often a person moves to different locations, also taking into account the use (or lack) of equipment or personal assistance. Considering the spatial context of mobility and the dependency on contextual factors, the LSA can also reflect participation in the society and the presence of adequate material and social environment [57, 101].

Robust evidence on the cost-effectiveness of frailty interventions is scarce [85], especially for multifactorial, interdisciplinary approaches in primary care based on existing healthcare structures [16]. An economic evaluation, as will be conducted in this study, has been recommended as one of the most urgently required strategies to close the gap between evidence and clinical practice [16]. Results of the cost-effectiveness analysis will indicate whether the effacts gained by the PromeTheus program outweigh the associated costs.

The study also includes a process evaluation to collect information that will be essential for further large-scale implementation of the PromeTheus program into routine care. Results of the process evaluation will provide a detailed understanding of facilitating and hindering factors for the delivery and outcomes of the complex program, enhance the external validity of the study findings, and identify recommendations for potential adaptions to increase the likelihood of successful implementation into routine care. All this will contribute to increasing the value of the evidence generated by the study for policy and practice [15].

In summary, this study will provide insight into the (cost-)effectiveness and implementation of a multifactorial, interdisciplinary intervention designed to prevent functional and mobility decline in (pre-)frail older adults in the community. If the PromeTheus program is shown to be (cost-)effective, there are major potential benefits to (pre-)frail older adults and the healthcare system. Preventing physical and mobility decline could reduce adverse health outcomes, such as frailty, disability, social isolation, and poor quality of life [1, 17, 102–105], and associated healthcare costs [8, 9, 106]. We thus expect that preserving physical functioning and mobility will contribute to maintain independence, reduce the needs and costs for care, and enable more participation and greater quality of life. As the PromeTheus program makes use of healthcare structures already available in all federal states (e.g., GPs, physiotherapists, service providers with counseling services), it is readily transferable to German healthcare for (pre-)frail older adults on a large scale.

### Trial status

Registration of GPs to participate in the PromeTheus study has been ongoing since January 2021.The official start of participant recruitment was May 2021; enrollment of the last participant is planned for April 30, 2022. By the time of submission (November 2, 2021), *n* = 86 participants have already been enrolled in the trial.

## Data Availability

The de-identified datasets generated and/or analyzed during the current study may be made available from the corresponding author upon reasonable request once the study has been completed.

## Abbreviations

AOK: ‘Allgemeine Ortskrankenkasse’ (health insurance company)
CFS: Clinical Frailty Scale
CG: control group
DEMMI: de Morton Mobility Index
EARS: Exercise Adherence Rating Scale
FIMA: ‘Fragebogen zur Inanspruchnahme medizinischer und nicht-medizinischer Versorgungsleistungen im Alter’ (questionnaire on the use of medical and non-medical care services in old age)
FIT: Frailty Intervention Trial
GP: general practitioner
IG: intervention group
LLFDI: Late-Life Function and Disability Instrument
LLFDI-FC: Late-Life Function and Disability Instrument – Function Component
LSA: Life-Space Assessment
MNA-SF: Mini Nutritional Assessment – Short Form
PROM: person-reported outcome measure
SNAQ: Simplified Nutritional Appetite Questionnaire
SOMCT: Short Orientation-Memory-Concentration Test
TIDieR: Template for Intervention Description and Replication
WEBB: Weight-bearing Exercise for Better Balance
